##### Acute kidney injury

Previous episodes of acute kidney injury may influence the decision to prescribe an anticoagulant and which anticoagulant to prescribe. Read codes for acute kidney injury will be counted as discrete events where they occur ≥1 week apart.

#### 
*​*Hepatic disease

Hepatic disease is an independent risk factor for bleeding and also affects the metabolism of warfarin, so it may affect the decision to prescribe anticoagulation. Hepatic disease will be defined as specified under the HAS-BLED section.

#### ​Previous bleed

Previous bleed includes any non-traumatic bleeding or haemorrhage. Bleeds will be divided in to subsections of major bleeding and clinically relevant non major bleeding (as described in HAS-BLED section), and also by site of bleed (intracranial bleeds, gastrointestinal bleeds or others).

#### 
*​*Dementia

Dementia include dementia (any type), Alzheimer’s disease and anyone prescribed an acetylcholinesterase inhibitor or memantine and excludes cognitive impairment where there is no diagnosis of dementia.

#### ​History of or at risk of falls

This includes any type of fall and any Read code which specifically indicates the practitioner is concerned that the patient is at risk of falling and excludes gait disturbances and other factors which may increase risk of falling but have not been defined by the GP as causing concern regarding falls risk.

#### 
*​*Fragility fractures

Fragility fractures are defined by the NICE as “…most commonly in the spine (vertebrae), hip (proximal femur) and wrist (distal radius). They may also occur in the arm (humerus), pelvis, ribs and other bones”.^21^ It is often not recorded in CPRD whether a fracture is thought to be a fragility fracture or not. Read codes for a diagnosis of fracture or operation to repair a fracture occurring in the spine, proximal femur, long bones, distal radius, humerus, pelvis or ribs will be included. Non-specific codes for osteoporotic and fragility fractures will also be included. Pathological fractures (unless specified that they are due to osteoporosis) will be excluded.

#### ​Heart valve replacements and mitral stenosis

Historically, AF patients have been classed as having valvular or non-valvular AF, but definitions of these have varied.^22^ The licensing for DOACs in the UK states they should only be prescribed for patients with non-valvular AF, however, the randomised controlled trials for the DOACs all defined valvular AF differently and exclusion criteria varied.^23^ Recently updated European Society of Cardiology guidelines suggest that VKAs should be the preferred option for patients with mechanical heart valves or moderate to severe mitral stenosis.^4^ This co-variate has been included to investigate what proportion on DOAC and warfarin users have a history of mechanical heart valves or Read codes for moderate or severe mitral stenosis.

#### 
*​*Number of general practice encounters

The number of encounters with healthcare professionals from general practice in the year prior to study entry, the year preceding the OAC index date or preceding the end of the time period will be used as an indicator of healthcare use.

### Statistical analysis

#### Objective 1: to describe changes in the point prevalence and incidence of OAC prescribing by year prior to the introduction of DOACs (2003–2007), between the introduction of DOACs and the time they were recommended by NICE for stroke prevention in AF (2008–2012), and following NICE recommendation (2013–2017).

Only patients prescribed an OAC will contribute data to the incidence and prevalence calculations. For incidence, patients may only contribute to either the warfarin or the DOAC group once as they will be censored at the time they are prescribed an OAC. The point prevalence will be calculated at the midpoint of each year so will take account of switching. For prevalence, a patient could contribute to the warfarin group for some years, and the DOAC group for other years. Prescription mapping will be used to calculate the number of people with an OAC prescription that includes that time point as the numerator and the total number of people in the cohort at that time point as the denominator.

The incidence of OAC prescribing will be calculated overall and for each specific OAC. Everyone in the cohort will be considered ‘at risk’ until the time they receive their first OAC prescription. Incidence will be calculated using the number of incident OAC users as the numerator and person-time at risk for non-exposed persons as the denominator. For the person-time at risk calculation, the denominator will be truncated at the date of their first OAC prescription. Incidence will be stratified by age (75–84 and 85+) and sex.

Figure 2 illustrates how patients may contribute to the incidence and prevalence calculations throughout the study.

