**Methods and analysis:**

A retrospective cohort study design will be used. Patients with a diagnosis of AF will be identified from the Clinical Practice Research Datalink (CPRD). The study period will run from 1 January 2003 to 27 December 2017. Patients enter the cohort at the latest date of the start of the study period, first AF diagnosis, 75th birthday or a year from when they started to contribute research standard data. Follow-up continues until they leave the practice, death, the date the practice stops contributing research standard data or the end of the study period (27 December 2017). Exposure to OACs will be defined as ≥1 prescription issued for an OAC of interest during the study period. Patients issued an OAC in the year preceding study entry will be defined as ‘prevalent users’. Patients starting on an OAC during the study period will be defined as ‘incident users’. Incidence and prevalence of OAC prescribing, patient demographics and characteristics will be described during three time periods: 2003–2007, 2008–2012 and 2013–2017. Persistence (defined as the time from initiation to discontinuation of medication) with and switching between different OACs will be described.

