### Source population

The study period will start on 1 January 2003 and will end on 27 December 2017. The source population will consist of all patients in CPRD who have ≥1 Read codes for AF and have contributed a minimum of 12 months’ research standard data prior to entry into the cohort. To be eligible to join the study, patients need to have the following: a Read code for AF recorded during or any time prior to the start of the study period; evidence to support the diagnosis of AF, such as a second AF diagnosis at a later date, an echocardiogram or prescription for a rate limiting or antiarrhythmic medication in the 3 months before the AF diagnosis or anytime after; and age of ≥75 years at study entry.

Patients will enter the cohort at the latest of the following dates:

Start of the study period.First AF diagnosis.75th birthday.A year from the date they started to contribute research standard data.

Patients will be censored if they leave the practice, the practice stops contributing data, at their date of death or at the end of the study. For the incidence calculations and comparison of patient characteristics, patients will be censored when they are prescribed an OAC.

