### Exposure

The OACs of interest in this study are warfarin, dabigatran, rivaroxaban, apixaban and edoxaban. Warfarin is the only VKA included as it is the most commonly used VKA in the UK. Dabigatran, rivaroxaban, apixaban and edoxaban are the only DOACs licensed for the prevention of stroke in AF available during the study period.

All prescriptions for the OACs of interest that are issued following an AF diagnosis, during the study period and in the year prior to entry in to the study cohort will be identified.

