#### ​Incident and prevalent users

Exposure status will be defined at cohort entry as

‘No OAC’, where the patient had at least a year free of OAC prior to study entry and does not receive an OAC during the study period.‘Incident OAC users’, where the patient had at least a year free of OAC prior to study entry then was prescribed an OAC during the study period.‘Prevalent OAC users’ if the patient received an OAC in the year prior to study entry.

Exposure status for incident OAC users will be stratified at the start of each study period to no OAC, warfarin or DOAC.

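### Yearly incidence pools newly diagnosed and long-standing untreated AF, so the crude trend alone cannot show a change in prescribing practice

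*Protocol article*

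**What the plan says.** **Who is in the cohort.** The Source population section requires "a Read code for AF recorded during or any time prior to the start of the study period". The abstract sets the entry date: "Patients enter the cohort at the latest date of the start of the study period, first AF diagnosis, 75th birthday", or one year after the start of research standard data. Only one of these four routes is a new diagnosis. The other three can bring in AF of any age.

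**Who is at risk.** Under Objective 1, "Everyone in the cohort will be considered ‘at risk’ until the time they receive their first OAC prescription". The rate is defined as follows: "Incidence will be calculated using the number of incident OAC users as the numerator and person-time at risk for non-exposed persons as the denominator".

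**How the rate is split.** "Incidence will be stratified by age (75–84 and 85+) and sex". Rates are also given overall, for each specific OAC and by year. Time since AF diagnosis is not a stratum here, and it is not among the covariates defined for Objective 3.

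**What the trend is for.** The strengths and limitations list says that examining changes over time will reveal changes in OAC prescribing practice since DOACs arrived. The Introduction asks whether DOACs altered prescribing rates in people aged 75 and over.

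**The concern.** A patient diagnosed last month and a patient left untreated for ten years contribute the same kind of person-time. If the chance of starting an OAC is much higher soon after diagnosis, the crude rate is a weighted average of a high and a low rate. The weights depend on how many patients are newly diagnosed and how large the stock of long-untreated patients is. Over 15 years either can change for reasons unrelated to prescribing, such as more case-finding.

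A rise between 2008–2012 and 2013–2017 could then be read as an effect of DOACs when it partly reflects a different mix of patients. A falling share of new diagnoses could hide part of a real rise. Age band and sex do not capture this. Objective 3 has a related gap: starters and non-starters may differ in time since diagnosis, and the planned tables would not show it.

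**Working it through.** The article gives no incidence rate, so there is no planned figure to reproduce. What follows is an illustration, and every rate in it is assumed.

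**1. Structure.** Let p be the share of at-risk person-time that falls early after diagnosis, with initiation rates h_E (early) and h_L (late). Then

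crude rate = h_L + (h_E − h_L) × p.

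With h_E and h_L fixed (prescribing unchanged), the crude rate still moves with p unless h_E = h_L.

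**2. Assumed inputs.** h_E = 100 per 100 person-years (PY), h_L = 5 per 100 PY, and death 12 per 100 PY. The early phase averages 3 months, so patients leave it at 4 per year. All inflow is newly diagnosed and untreated, and the model is in steady state before 2003.

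**3. Baseline, per unit inflow.**
- Early pool: E = 1 / (1.00 + 0.12 + 4) = 0.1953
- Late pool: L = 4 × 0.1953 / (0.05 + 0.12) = 4.596
- p = 0.1953 / (0.1953 + 4.596) = 4.08%
- Crude rate = 5 + 95 × 0.0408 = 8.9 per 100 PY

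**4. Change only the number of diagnoses, I(t).** The pools follow dE/dt = I(t) − 5.12E and dL/dt = 4E − 0.17L, stepped through 2003–2017.

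| Diagnoses (prescribing unchanged) | Year | p | Crude rate per 100 PY |
|---|---|---|---|
| Constant | any | 4.08% | 8.9 |
| +50% from 2013 | 2013 | 5.48% | 10.2 |
| +50% from 2013 | 2017 | 4.82% | 9.6 |
| −3% a year from 2003 | 2017 | 3.45% | 8.3 |
| +6% a year from 2003 | 2017 | 5.33% | 10.1 |

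The 2013 step is 10.21 / 8.87 = 1.15, an apparent 15% rise with no change in prescribing.

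**5. Dependence on the key assumption.** The same 50% step in diagnoses was repeated with other early rates.
- h_E = 25 per 100 PY: 5.8 to 6.1 (+5%)
- h_E = 200 per 100 PY: 13.0 to 15.8 (+22%)
- h_E = h_L = 5 per 100 PY: no movement

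**6. A differently built model.** Here the early phase is the first year. With initiation of 60 then 5 per 100 PY and exit of 15 per 100 PY, the crude rate is flat at 18.1 with constant diagnoses. It rises to 19.6 or 21.0 by 2017 if diagnoses grow 3% or 6% a year. Over early rates of 30–100, late rates of 3–10, exit of 10–15 per 100 PY and growth of −3% to +6% a year, without former users, the 2017/2003 ratio of crude rates runs from 0.86 to 1.28.

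**7. Within strata.** In both models the rates within strata of time since diagnosis are constant by construction when prescribing is constant. Stratifying removes this movement.

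**The case against.** The strongest reply is that Objective 1 is descriptive. A first-OAC rate among all untreated patients aged 75 and over is well defined and relevant: the Introduction starts from underuse, and treating people who had been passed over for years is part of the story. Point prevalence is also planned and does not depend on this risk set. The article nowhere says that initiation clusters at diagnosis, and extra strata can be left to a fuller document.

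Much of this stands. The crude rate is not wrong and should be kept, and newly diagnosed AF need not become the main measure. It does not remove the point, because the article names the strata it will use and intends the trend to show changed practice. Prevalence does not measure initiation.

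Some stronger readings are tempting but not supported:

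- **Prevalent users inflate the denominator.** A reader might infer this from the word everyone. However, a prevalent user is so classed "if the patient received an OAC in the year prior to study entry", those earlier prescriptions are retrieved, and person-time is cut at the first prescription and limited to non-exposed persons. The natural reading is that these patients are already outside the denominator.
- **The one-year washout creates a false fall.** Patients who stopped more than a year before entry can count as incident. The direction of any drift depends on an unknown restart rate. Against a baseline of 8.9, the modelled 2003 rate is 8.0, 9.1 or 10.7 at restart rates of 0.05, 0.10 or 0.25 a year. That model also ignores former users who enter after 2003.
- **The crude rate is biased because it responds weakly to more prescribing at diagnosis.** If only early initiation rises, the rate among all untreated patients truly rises by less.
- **Incident should mean never treated.** OAC prescriptions are sought only "during the study period and in the year prior to entry in to the study cohort will be identified". Never-use would need a longer look-back, and its meaning would vary with record length.
- **Objective 3 compares mostly new with mostly old AF.** The documents give no figures for this.

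**Conclusion.** The point holds as a limit on interpretation with an inexpensive remedy, not as an error in the rate. The planned strata leave time since diagnosis uncontrolled, so the crude yearly trend cannot by itself separate a change in prescribing from a change in case mix.

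Under the assumed rates, the movement without any prescribing change is 8.9 to 10.2 per 100 PY for a 50% rise in diagnoses, and 8.3 to 10.1 by 2017 for growth of −3% to +6% a year. These figures rest on initiation being concentrated near diagnosis and on the mix changing over time. If either fails, the shift is nil. Neither its size nor its direction in the real cohort can be derived from the article.

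**What to change.** - **Objective 1:** keep the planned crude rate. Add yearly incidence stratified by time since first AF code, for example <3 months, 3–12 months and >12 months, splitting each patient's person-time at those boundaries. State that the before/after trend will be read within strata.
- **Objective 3:** show the comparison by the same split, with time since first AF code taken at the date already used for comorbidities (OAC index date for starters, end of the time period for the no-OAC group).
- **Optional clarification:** one sentence under Objective 1 saying that prevalent users, as defined under Incident and prevalent users, are excluded from the incidence denominator.

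**Cost:** extra strata in tables and a few sentences. No new data are needed, because the first AF date already helps to set cohort entry. Intervals will be wider within strata, most of all where the <3 months group is further divided by year, age band, sex or specific OAC.

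### Objective 1 stratifies incidence by age and sex but defines point prevalence only as an overall ratio, so the 15-year prevalence trend can mix change in prescribing with change in the cohort's age-sex mix

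*Protocol article*

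**What the plan says.** Objective 1 sets out to describe yearly change in two measures, point prevalence and incidence of OAC prescribing, across three periods around the arrival of DOACs.

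- **Prevalence** (Statistical analysis, Objective 1). Timing: "The point prevalence will be calculated at the midpoint of each year so will take account of switching". Numerator: "Prescription mapping will be used to calculate the number of people with an OAC prescription that includes that time point as the numerator". Denominator: "the total number of people in the cohort at that time point as the denominator". The only split described is by drug group, warfarin or DOAC.
- **Incidence** (same section): "Incidence will be stratified by age (75–84 and 85+) and sex". The sentence names incidence alone.
- **Cohort** (Source population): "The study period will start on 1 January 2003 and will end on 27 December 2017". Patients join at the latest of four dates, one of which is "A year from the date they started to contribute research standard data". On exit: "Patients will be censored if they leave the practice, the practice stops contributing data, at their date of death", or at study end.
- **Age and prescribing** (Introduction): advancing age is among the reasons physicians give for being less likely to prescribe vitamin K antagonists in AF.
- **Use of the result**: the strengths and limitations box says the study will show whether prescribing practice has changed since DOACs arrived. The Introduction asks whether OAC prescribing rates in people aged 75 or over have changed.

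**The concern.** A yearly overall proportion is a weighted mean of the proportions in its age-sex groups, and the weights are that year's cohort composition. In an open cohort followed from 2003 to 2017 nothing holds those weights constant. If treatment differs by age, as the Introduction leads one to expect at least for vitamin K antagonists, a change in the 85+ share moves the overall figure even when prescribing within each band has not changed. A real change within bands can equally be hidden.

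The authors evidently think age and sex matter to Objective 1, since they stratify incidence by both. The same reason applies to prevalence. At stake is the before-and-after statement about how many older people with AF are anticoagulated. From the overall series alone, a reader could not tell how much of a rise, fall or plateau is prescribing and how much is composition.

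**Working it through.** The article states no prevalence, age mix or cohort size, so there is no figure to reproduce. The check has two parts.

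**1. Does anything else in the plan separate the two sources of change?**

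- Stratified incidence measures starting treatment among unexposed people. It does not measure current use.
- Objective 3 reports age and sex, but by five-year period and without prevalent users. Its tables therefore leave out people who are in the prevalence numerator and cannot give the yearly age mix of the prevalence denominator.
- The statement that CPRD is representative of the UK population does not fix the age mix of this AF cohort over time.
- The planned 95% CIs cover sampling error, not composition.

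So nothing in the article does so.

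**2. How large could the effect be?** All inputs here are assumptions.

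Let p1 and p2 be prevalence at 75–84 and 85+, and s the 85+ share.

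Crude prevalence = p1(1 − s) + p2·s. With p1 and p2 unchanged, the change between years = −(p1 − p2) × (change in s).

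Worked case, p1 = 55%, p2 = 35%, s from 30% to 40%:

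- Start: 0.70 × 55 + 0.30 × 35 = 49.0%
- End: 0.60 × 55 + 0.40 × 35 = 47.0%
- Crude change −2.0 points, with no change in either band.
- Standardised to the fixed 70/30 mix: 49.0% in both years, change 0.0.

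Size of the shift in points, over a range:

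| Gap p1 − p2 | s moves 5 points | 10 points | 15 points |
|---|---|---|---|
| 10 points | 0.5 | 1.0 | 1.5 |
| 20 points | 1.0 | 2.0 | 3.0 |
| 30 points | 1.5 | 3.0 | 4.5 |

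The shift is downward if the less-treated band grows and upward if it shrinks.

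Masking case: the same inputs, with a true rise of 2.0 points in both bands (57% and 37% at the end). Crude prevalence at the end = 0.60 × 57 + 0.40 × 37 = 49.0%, which looks flat. Standardised to 70/30 it is 0.70 × 57 + 0.30 × 37 = 51.0%, which shows the rise.

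**Yardstick.** A change between two years must be set against the precision of a difference. Treating the years as independent, with prevalence near 50% and n patients per year, the 95% half-width = 1.96 × √(2 × 0.25/n):

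- n = 10,000: 1.4 points
- n = 20,000: 1.0 point
- n = 50,000: 0.6 points

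At 20,000, a shift of 0.5 lies inside sampling error, shifts of 1.0 are at its edge, and the rest of the table exceeds it.

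**The case against.** The strongest reply is that the objective is descriptive. The proportion of AF patients aged 75 or over who are anticoagulated in a given year is a proper quantity, and if the cohort ages, that is part of what is being described. This stands: the overall series is not wrong and should be kept. It does not answer the point about trend, because the article intends to use the series to show change in prescribing practice.

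A second reply is that this is a condensed article. It never says that prevalence will be reported only crude. That is inferred from the formula and from the absence of any strata, and the full protocol may add them. This stands in part. But the article does specify strata, and it assigns them to one of two paired measures. That asymmetry is in its own text.

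Third, every number in the illustration is assumed, including the direction. This stands in full.

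A reader might also infer that practice turnover distorts the prevalence trend, since follow-up can end at "the date the practice stops contributing research standard data" and practices can also begin contributing. The documents do not support going that far. Nothing in them says that prescribing differs between practices or that turnover was selective, and turnover would affect incidence in the same way. It remains a possibility worth a sensitivity analysis.

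**Conclusion.** The point holds as a limit on what the prevalence trend can show. Incidence has age and sex strata, prevalence has none stated, the cohort is open over 15 yearly snapshots, and nothing else planned separates composition from prescribing.

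Under assumed band gaps of 10 to 30 points and an 85+ share moving by 5 to 15 points, the compositional shift is 0.5 to 4.5 points in either direction, against about 1.0 point of sampling error for a two-year difference at an assumed 20,000 patients per year. Much of that range would therefore look like real change. The actual size and sign cannot be established from the article.

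It would be tempting to conclude that the planned trend will be biased, or that an ageing cohort will make it understate uptake. The article gives no age mix or age-specific prevalence, so neither conclusion is supported. The age statement in the Introduction also concerns physicians' stated reasons about vitamin K antagonists, and does not extend to all OACs. Nor does the article make prevalence the primary measure.

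**What to change.** In Statistical analysis, Objective 1:

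1. Extend the existing strata to prevalence: report yearly point prevalence at 75–84 and 85+, using age attained at the mid-year date, and by sex.
2. Beside the crude yearly series, report overall prevalence and incidence directly standardised to one fixed age-sex distribution, named in advance (for example the cohort at mid-2010).
3. Optionally, repeat both measures in practices that contribute throughout the study period, as a sensitivity analysis.

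Items 1 and 2 use data already held and change no eligibility, exposure or outcome definition. The cost is a few sentences, some extra tables and wider CIs within strata. Item 3 has two drawbacks: a smaller sample with wider CIs, and a selected set of practices that may be less representative than the whole database. It should support the main series and not replace it.
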